Patients with any of the following conditions are not eligible for both the currently depressed and remitted depressed groups: (1) woman who is pregnant (test at enrolment), parturient, or lactating, (2) persons deprived of their liberty by judicial or administrative decision, (3) persons unable to express consent, (4) subjects with an identified neurodegenerative condition or a psychiatric pathology other than MDD (bipolar disorder, chronic psychotic disorder, addictive disorder except for nicotine, obsessive-compulsive disorder, post-traumatic stress disorder), (5) subjects with a history of stroke, (6) subjects with an acute infectious pathology, or chronic or acute inflammatory diseases, (7) subjects with a history of autoimmune diseases, (8) subjects receiving long-term anti-inflammatory and immunosuppressive therapy, (9) subjects with antipsychotic treatment in the last 3 weeks prior to enrolment, (10) subjects with a prescription of diazepam, midazolam, chlordiazepoxide in the last week prior to enrolment, (11) subjects with contraindications to MRI or PET imaging, (12) subjects who refuse to be informed of an abnormality detected during MRI examination.

The exclusion criteria for the control group are: (1) a significant history of psychiatric or somatic disorders, (2) a current mental disorder, (3) an active suicidal risk, (4) an ongoing psychotropic treatment.

Depressed patients will be recruited throughout 4 centers (Bordeaux, Montpellier, Tours, and Toulouse) of the French network from 13 expert centers for resistant depression (50). The subjects of the control group will be included at clinical investigation sites working locally in close collaboration with each participating expert center.

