### PET assessment

The ^18^F-DPA-714 and ^18^F-FEPPA molecules are two second radiotracers that target TSPO (overexpressed microglial receptor with inflammation) (55, 56). These two tracers cross the blood-brain barrier (BBB) and have a good affinity for TSPO (57, 58). The ^18^F-DPA-714 tracer is metabolized rapidly and some metabolites secondary to oxidation can cross the BBB in small amounts (59). The FEPPA tracer is also metabolized but its hydrophile metabolites do not cross the BBB (57). The amounts of injected activity and the effective patient dose are comparable between the two tracers (47, 60–62). The ^18^F-DPA-714 tracer has been studied extensively in humans as well as in preclinical models (51 references on Medline) (46–49). There is less information on the use of FEPPA (14 references on Medline, only 8 clinical studies).

Articles on the FEPPA use in humans mention an acquisition time of 125 min, which is difficult to achieve with a large number of subjects and is very uncomfortable for patients who must be immobile during these 125 min. For FEPPA, the data analysis is performed on a kinetic model with two compartments and arterial blood samples must be collected from the patient to measure the input function of the radiotracer (62). The main advantage of using ^18^F-DPA-714 is its acquisition and analysis protocol. The radiotracer is injected (200 MBq) and then a 30-min acquisition is performed 1 h after the injection. The analysis consists of calculating a standardized uptake value (SUV). Some studies have shown that using this semi-quantitative analysis method and using a reference region results in less variability than studies using a kinetic model (49). Since ^18^F-DPA-714 appears to be the preferred tracer for studying neuroinflammation on PET, it will be used in this study.

In addition, there is known a genetic polymorphism for TSPO. This polymorphism determines the tracer′s affinity for TSPO, with some persons having high affinity sites, mixed affinity sites or lower affinity sites. The two radiotracers (^18^F-DPA-714 and ^18^F-FEPPA) are both impacted by this genetic polymorphisms (63). For feasibility reasons, the TPSO genotype of subjects cannot be an inclusion criterion; nevertheless, this parameter will be taken into account during the data analysis as a covariate, allowing us to weigh the PET imaging data based on whether the individuals have high or low affinity sites.

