### Risk benefit balance

No direct individual benefit can be expected for subjects participating in this study. The therapeutic modalities used in these patients will not be altered by their participation in the study or by the results. Strict compliance with the inclusion and exclusion criteria will ensure there are no foreseeable risks for persons participating in this study. The imaging modalities used (MRI and PET) do not involve any foreseeable risk when patients presenting a contraindication to one or other of these examinations are not included according to the aforementioned inclusion/exclusion criteria. The principal investigator must constantly monitor, assess, and document risks and ensure that they can be managed satisfactorily.

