### Experimental procedures (Table 1)

#### Preselection

Patients in both the currently depressed and remitted depressed groups will be preselected during their medical follow-up within each participating research site. Investigators will inform the patient and answer all questions about the purpose, nature of constraints, foreseeable risks, and expected benefits of the present research. They will also specify the rights of the patient regarding research and will verify the eligibility criteria. A copy of the Information/Consent form will then be given to the patient. Healthy volunteers for the control group will be invited by phone to participate into the study by a Clinical Investigation Centre clinical research associate. A copy of the information leaflet will be sent to them, giving them sufficient time to consider their participation.

**Table 1 T1:** Summary of INFLADEP design.

	**Preselection**	**Enrolment visit D0**	**Assessment visit D7 (± 5 days)**
Patient information	✓	✓	
Collection of informed consent		✓	
Clinical examination^1^ – Validation of eligibility criteria		✓	
Collection of blood samples^2^		✓	
MRI examination			✓
PET examination			✓
Questions about concomitant treatments		✓	✓
Search for AE/SAE		✓	✓

1 *Clinical examination: discussion with doctor, MADRS, BAS, C-SSCR, MINI surveys*.

2 *To measure CRP levels in healthy volunteers and biological markers (TNF-alpha, IL-6), TSPO phenotype in all subjects, beta-HCG for women of childbearing age*.

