#### Enrolment visit

After obtaining the subject′s consent, a clinical examination will be performed to verify the eligibility criteria of the potential study participants along with the collection of psychiatric and somatic history, and current treatments. This clinical examination will include MINI (Mini International Neuropsychiatric Interview) (Appendix 5), which consists of a short, structured clinical interview that allows investigators to diagnose past and current psychiatric disorders according to the DSM (65), which is an exclusion criterion for subjects in the control group. This visit will also involve conducting psychometric assessments (MADRS, BAS, C-SSCR).

A blood sample will be taken to measure hs-CRP levels (inclusion criterion for the control group). This sample will also be used to measure IL-6 and TNF-alpha if the subject is included in the study. All the samples will be taken in the morning to take into consideration, as much as possible, the effects of circadian rhythm on circulating inflammatory biomarkers. Thereafter, an appointment will be scheduled for the assessment visit depending on the availability of the subject and the different technical platforms, at 7 ± 5 days following the inclusion visit.

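### Minor safety point: the printed pregnancy test is timed at enrolment and can be 2 to 12 days old when the PET tracer is injected

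*Protocol article*

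**What the plan says.** - **Timing of the test.** In the Protocol article, Eligibility criteria, exclusion (1) for the two depressed groups reads "woman who is pregnant (test at enrolment), parturient, or lactating".
- **Where it sits in the schedule.** Footnote 2 of Table 1 (Experimental procedures) lists what the blood sample is for, including "TSPO phenotype in all subjects, beta-HCG for women of childbearing age". The blood-sample row has a single tick, at D0, and the Enrolment visit section also places the sample there.
- **When exposure occurs.** The Enrolment visit section books the assessment visit "at 7 ± 5 days following the inclusion visit". PET and MRI are ticked only at that visit. The PET assessment section gives an injected activity of 200 MBq.
- **What is repeated at the assessment visit.** Two other rows are ticked at both visits: "Questions about concomitant treatments" and "Search for AE/SAE".
- **How safety is argued.** The Risk benefit balance section states "No direct individual benefit can be expected for subjects participating in this study", and also "Strict compliance with the inclusion and exclusion criteria will ensure there are no foreseeable risks for persons participating in this study".

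**The concern.** The pregnancy test is there to prevent fetal exposure to the tracer, so the date that matters is the injection date, not the enrolment date. As printed, a site can follow the schedule exactly and inject a woman whose only recorded negative test is up to 12 days old. Women are eligible from age 25, so some participants will be of childbearing age.

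The Risk benefit balance section rests its assurance on compliance with the entry criteria. For pregnancy, compliance with the printed timing leaves a gap that is cheap to close. Because participants gain nothing directly from the scan, no benefit offsets an avoidable exposure. What is at stake is participant safety on a small scale; sample size, power and the PET comparison are untouched.

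**Working it through.** **Step 1. The interval, from the document.** The visit is at 7 ± 5 days after D0.
- Shortest gap: 7 − 5 = 2 days
- Nominal gap: 7 days
- Longest gap: 7 + 5 = 12 days

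With a test on the scan day before injection, the gap is 0 days.

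**Step 2. Is a later check printed elsewhere?** Three provisions could be read that way.
- Exclusion (11), contraindications to MRI or PET, is an entry criterion. Table 1 ticks validation of eligibility at D0 only, and no test is attached to this criterion.
- The safety checks in the Assessment visit section are the MRI technician's and are described for the MRI.
- The investigator's duty to monitor risk, in the Risk benefit balance section, is general and schedules nothing.

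None of them supplies a pregnancy test before injection.

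**Step 3. Expected yield of a scan-day test.** The document gives no conception rate. Assume a constant rate r of 0.005 to 0.02 per woman per 30 days. Let g be the gap in days and L the test's detection lag. The uncovered window is L + g with a D0 test only, and L with a scan-day test of equal sensitivity. The difference is g, so:

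- extra pregnancies found per woman = r × g / 30
- tests per extra pregnancy = 30 / (r × g)

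| Gap g (days) | Extra found per woman | Tests per extra pregnancy |
|---|---|---|
| 2 | 0.0003–0.0013 | 750–3000 |
| 7 | 0.0012–0.0047 | 214–857 |
| 12 | 0.002–0.008 | 125–500 |

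L cancels, so these figures do not depend on it. Pregnancies too early to detect on the scan day stay undetected.

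**Step 4. Expected number in this study.** As a ceiling, suppose all 60 subjects were women of childbearing age at the highest assumed rate. At 7 days this gives 60 × 0.02 × 7/30 = 0.28. If 30 of the 60 were (an assumption), the range at 7 days is 30 × 0.005 × 7/30 = 0.035 to 30 × 0.02 × 7/30 = 0.14.

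**Step 5. A less sensitive test.** If a urine test turns positive d days later than the D0 blood test, replace g by g − d. With d = 2 (an assumption), the gain at the 2-day gap is zero. At the nominal gap it is 5 days, or 30/(0.02 × 5) = 300 to 30/(0.005 × 5) = 1200 tests per extra pregnancy.

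**The case against.** The strongest reply is that this is a condensed article. The Assessment visit section describes the MRI session and says almost nothing about PET-day procedure, so a pre-injection check could have been dropped along with everything else. Table 1 is captioned as a summary and is demonstrably incomplete: the Eligibility criteria require plasma antidepressant levels in the therapeutic range, yet neither the table nor its footnotes list that assay. Stating that an entry criterion is tested at enrolment does not say that no later check is made. The yield is also tiny and rests on a rate from outside the document.

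Much of this stands. A reader might infer that the study injects women with no pregnancy check on the scan day. The documents do not support that, because the full protocol or routine nuclear-medicine practice may require one. The contrast in Table 1 between one-off and repeated rows is only weak evidence: beta-HCG has no row of its own, and a urine test would not belong in the blood-sample row.

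A reader might also infer that pregnant controls are admissible, since the printed control-group exclusions do not name pregnancy. That too goes beyond the text. Footnote 2 does not confine beta-HCG to patients, and the control list also leaves out imaging contraindications, so it looks abbreviated.

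The reply does not remove the point that the article goes beyond silence. It gives a time for the test, consistently in the exclusion criterion and in the schedule, and that time is earlier than it need be.

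**Conclusion.** The point holds as a minor participant-safety improvement. The 2 to 12 day gap follows directly from the printed schedule. The absence of a later check is established only for the article.

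The size is small: on the assumed conception rates, well below one expected event among at most 60 subjects. The yield assumes a constant rate and a scan-day test as sensitive as the D0 blood test; a less sensitive one gains little or nothing at the shortest gap. No fetal dose or harm has been estimated.

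The case rests on the low cost of the remedy and the lack of direct benefit to participants, not on frequency. It would be wrong to read it as a serious safety failure or as a threat to the trial's results.

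**What to change.** 1. Change the parenthesis in exclusion (1) to: *test at enrolment and on the day of PET before injection*.
2. In Table 1, add an hCG test to the assessment-visit column for women of childbearing age in all three groups, and require a negative result before injection. Choose a sensitive assay.
3. State that the pregnancy exclusion applies to controls as well as patients.

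If the full protocol already contains these provisions, the only change needed is to align the article's table and wording.

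The cost is one inexpensive test per woman of childbearing age, at a visit she already attends, plus a minor wording amendment.

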## Subjects and methods

### Subjects

Our study will compare data collected in patients with moderate to severe MDD (“currently depressed group”, *n* = 20) treated unsuccessfully with classical antidepressants (SSRIs, SNRIs) before the initiation of a new antidepressant treatment according to good practice recommendations, with those included in two other study groups, comprising:
- non-depressed healthy volunteers (“control group”, *n* = 20), which enables us to control both the depression factor and the treatment factor for the characterization of neuroinflammation. They will be matched on age and gender to the experimental group of currently depressed patients;- depressed patients reaching clinical remission (“remitted depressed group”, *n* = 20) and still being treated with antidepressants, which allows us to control the depression factor. We hypothesize that the presence of an effective antidepressant treatment will contribute to demonstrate a significant decrease in neuroinflammation in those depressed patients. This group will be matched to the currently depressed group according to the class of antidepressant treatments (SSRIs, SNRIs), as well as age and gender.

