### Eligibility criteria

The following inclusion criteria will be applied to all study groups: (1) men and women aged 25 to 55 years, (2) affiliated to a Social Security scheme, (3) able to understand the given instructions and information about the study design, and (4) have provided written informed consent. The currently depressed group will include patients: (1) meeting the DSM-5 criteria of MDD diagnosis, (2) experiencing significant depressive symptoms (as indicated by a score > 20 on the Montgomery and Asberg Depression Rating Scale, MADRS), (3) receiving an ineffective antidepressant treatment (a well-conducted treatment at an appropriate dosage for a minimum of 6 weeks), and (4) showing plasma antidepressant levels within the therapeutic range after at least 1 additional week of antidepressant treatment with unchanged dosage. The remitted depressed group will comprise patients: (1) meeting the DSM-5 criteria of MDD diagnosis, (2) achieving remission for at least 8 consecutive weeks according to the standard DSM-5 criteria (as indicated by a MADRS score <10), and (3) receiving antidepressant medications at a stable dosage for 1 week or more. The control group will include normal healthy subjects free from any current or past psychiatric conditions and without peripheral signs of inflammation (as indicated by circulating concentrations of hs-CRP <5 mg/L).

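### The nicotine exemption is written for the two patient groups only, so on a plain reading nicotine dependence can occur in patients but not in controls, and neither the control matching nor the primary model offsets this

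*Protocol article*

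**What the plan says.** All references are to the protocol article.

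- **Patients (Eligibility criteria).** The list of conditions that "are not eligible for both the currently depressed and remitted depressed groups" includes "a psychiatric pathology other than MDD (bipolar disorder, chronic psychotic disorder, addictive disorder except for nicotine" and further diagnoses. Addictive disorder is thus treated as a psychiatric pathology, and nicotine is expressly taken out of it for both patient groups by the words "addictive disorder except for nicotine".
- **Controls (Eligibility criteria).** The inclusion rule is: "The control group will include normal healthy subjects free from any current or past psychiatric conditions". The separate control exclusions begin: "1) a significant history of psychiatric or somatic disorders, (2) a current mental disorder". Neither rule carries a nicotine exemption, and neither names nicotine, tobacco or smoking.
- **Matching (Subjects).** For controls: "They will be matched on age and gender to the experimental group of currently depressed patients". The remitted group is matched to the currently depressed group "according to the class of antidepressant treatments (SSRIs, SNRIs), as well as age and gender".
- **Primary model (Analysis of PET imaging data).** A multivariate ANOVA of TSPO volume in 13 regions, with diagnosis and TSPO genotype as fixed factors.
- **Sample size (Study sample calculation).** 20 per group and 80% power, with reference to distribution volumes of 12.3 and 9.3 ml/cm³. No SD is given.

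**The concern.** The primary contrast is currently depressed patients against controls. The Subjects section relies on the control group to isolate the depression and treatment factors, so the two groups should otherwise be selected under the same rules. Here one exposure is let into one side and, on a plain reading, kept out of the other.

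If nicotine dependence or smoking shifts [18F]DPA-714 uptake, IL-6 or TNF-alpha, that shift enters the patient-versus-control difference and is labelled depression. The usual repair, a covariate, is weak for dependence itself while the rule stands: with no dependent controls, a dependence term would be estimated from patients alone. This is why the eligibility wording matters, and not only the model.

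**Working it through.** **Step 1. The rules side by side.**

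| | Currently depressed | Remitted | Control |
|---|---|---|---|
| Addictive disorder | excluded | excluded | excluded through the general psychiatric criteria |
| Nicotine exemption | yes | yes | none written |
| Matching | reference group | antidepressant class, age, gender | age, gender |
| Smoking in primary model | no | no | no |

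The two patient columns share the same nicotine rule, so current versus remitted has no rule-based asymmetry. The asymmetry lies in the contrasts of patients with controls, which include the primary one.

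**Step 2. The plan's own power figure.** The difference is 12.3 − 9.3 = 3.0 ml/cm³. Without an SD, the stated 80% can be neither confirmed nor refuted. Solving the two-sample t-test (noncentral t, two-sided 0.05, 20 per group) for 80% power gives a standardised difference d = 0.909, that is, an SD of 3.0 / 0.909 = 3.30 ml/cm³. The normal approximation gives an SD of 3.39 (d = 0.886). The two-sided level is an assumption, since the article states only P ≤ 0.05.

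**Step 3. Size of a possible bias.** The documents give no smoking rates and no smoking effect, so both inputs are assumptions.

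Bias (in SD) = excess share of exposed subjects among patients × shift per exposed subject (in SD).

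Power with an opposing shift is the t-test power at 0.909 − bias. The false-positive rate with no true difference is the rejection rate at a standardised difference equal to the bias.

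| Excess share | Shift (SD) | Bias (SD) | Power, opposing shift | False-positive rate |
|---|---|---|---|---|
| any | 0 | 0 | 80.0% | 5.0% |
| 0.30 | 0.25 | 0.075 | 72.9% | 5.6% |
| 0.40 | 0.25 | 0.10 | 70.3% | 6.1% |
| 0.30 | 0.50 | 0.15 | 64.8% | 7.5% |
| 0.40 | 0.50 | 0.20 | 58.9% | 9.5% |

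With an SD of 3.30, a bias of 0.075 to 0.20 SD is 0.25 to 0.66 ml/cm³, or 8% to 22% of the planned 3.0.

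**Step 4. A wider range.** With an excess share of 0.2 to 0.6 and a shift of 0.5 to 0.8 SD, the bias runs from 0.10 to 0.48 SD (0.33 to 1.58 ml/cm³, or 11% to 53% of 3.0). The false-positive rate is then 6% to 32%, and power under an opposing shift is 70% to 26%. The spread shows that the assumptions, not the protocol, set the size.

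These figures treat one outcome with a t-test. The planned primary test is a multivariate ANOVA over 13 regions, so they illustrate scale and do not predict that test's behaviour.

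**The case against.** The other side has several fair points.

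- **No control criterion names nicotine.** The bar is inferred from general psychiatric wording, and the control exclusion speaks only of a significant history. The Enrolment visit section applies the psychiatric exclusion through the MINI without saying whether nicotine dependence counts. This stands as a limit on certainty. The inference is still strong, because the article itself classes addictive disorder as psychiatric pathology and found it necessary to exempt nicotine for patients.
- **Dependence is not smoking.** A reader might infer that smoking differs between the groups by design. The text does not support that: non-dependent smokers may enter any group, and patients need not smoke. The rules permit an imbalance in dependence and do nothing to balance it; they do not fix a difference in smoking.
- **The remitted group.** A reader might extend the problem to every comparison among the three groups. That does not hold for current versus remitted, where the nicotine rule is the same and matching also covers antidepressant class.
- **No effect is documented.** Nothing in the article says that smoking alters the tracer signal or the cytokines. This stands: size and direction are unknown. For hs-CRP, the control contrast is in any case already shaped by the limit of 5 mg/L.
- **Articles leave detail to the full protocol.** Silence about a smoking question or a further covariate would not be a finding by itself. The point here rests on eligibility and matching rules that the article does state, and states unequally.

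**Conclusion.** The point holds in a limited form. As written, nicotine dependence is allowed in both patient groups and, on a plain reading, not in controls. Matching on age and gender and a model with diagnosis and genotype leave this uncorrected in the primary contrast. Any effect of nicotine dependence or smoking would be attributed to depression there.

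The size cannot be taken from the documents. On the assumptions in the first table it is 0.075 to 0.20 SD, enough to matter with 20 per group. If smoking does not affect these measures it is zero. The conclusion about the unequal rule does not depend on these figures or on the unverified 80% power. It does depend on reading the general psychiatric criterion for controls as covering nicotine dependence.

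**What to change.** 1. In the control criteria, apply the same nicotine rule as for the two patient groups, in explicit words. This removes the asymmetry and settles how investigators should read the general psychiatric criterion.
2. Record current smoking (yes/no) at the D0 visit in all subjects.
3. Include it with genotype in the patient-versus-control PET analyses and in the peripheral-marker analyses, at least as a sensitivity analysis. Once the same rule applies to all groups, the term no longer has to rest on patients alone by rule.
4. Balancing controls to the currently depressed group on smoking is optional, where recruitment allows. Matching the remitted group on smoking is not needed, since the asymmetry does not reach that comparison and a fourth matching factor would burden recruitment of 20 subjects.

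The cost is one wording change, one extra question at an existing visit and one degree of freedom in the models.
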